## Abstract

**Background:**

Epidemiological studies show an association between masticatory function and cognitive impairment. This has further strengthened the notion that tooth loss and impaired masticatory function may be risk factors for dementia and cognitive decline. Animal experiments have indicated a causal relationship and several possible mechanisms have been discussed. This evidence is, however, lacking in humans. Therefore, in the current interventional study, we aim to investigate the effect of rehabilitation of masticatory function on cognition in older adults.

**Methods:**

Eighty patients indicated for prosthodontic rehabilitation will be randomly assigned to an experimental or a control group. Participants will conduct neuropsychological assessments, masticatory performance tests, saliva tests, optional magnetic resonance imaging, and answer questionnaires on oral health impact profiles and hospital anxiety and depression scale before, 3 months, and 1 year after oral rehabilitation. The difference between the two groups is that the control group will be tested an additional time, (at an interval of about 3 months) before the onset of the oral rehabilitation procedure. The primary outcome is a change in measures of episodic memory performance.

**Discussion:**

Although tooth loss and masticatory function are widespread in older people, it is still an underexplored modifiable risk factor potentially contributing to the development of cognitive impairment. If rehabilitation of masticatory function shows positive effects on the neurocognitive function, this will have great implications on future health care for patients with impaired masticatory status. The present project may provide a new avenue for the prevention of cognitive decline in older individuals.

*Trial registration*: The protocol for the study was retrospectively registered in ClinicalTrials.gov Identifier: NCT04458207, dated 02-07-2020.

## Background

Dementia is a general term that encompasses several neurodegenerative diseases that affect approximately 7% of the population older than 65 years [1], and about 30% older than 80 years [2, 3]. The World Health Organization defines dementia as a “syndrome in which there is deterioration in memory, thinking, behavior, and the ability to perform everyday activities”. Studies have suggested a rapid rise in the incidence of dementia in the aging population [4, 5]. Since dementia is a chronic and progressive syndrome, its prevalence will also increase with the rise of the aging population. Further, with the increase in life expectancy, the global burden for the health care of individuals with dementia is expected to increase exponentially. Therefore, the steep rise in dementia is presenting a "significant and urgent challenge" to health care services, and interventions are needed to prevent and counter these challenges [6].

Current research has emphasized the concept of a “brain-stomatognathic axis” in relation to geriatric healthcare. Accordingly, this axis is the complex communication network between the cortical and subcortical regions of the brain and the stomatognathic/masticatory system [7–9]. Oral conditions such as loss of teeth [10, 11], chronic inflammatory disease such as periodontitis [12], and chewing difficulties [13] are commonly associated with the risk of neurodegenerative diseases [14–18]. Evidence from animal studies has further strengthened the associations and has suggested a causal relationship.

Studies on aged rats and mice conclude that a disturbance of normal mastication accelerates the age-dependent impairment of learning abilities and memory, combined with significant degenerative changes in the hippocampus [19, 20]. Specifically, the linkage between mastication and brain function in rodents has been studied by either altering the diet (i.e., hard food vs powder or liquid diet) [21], alteration of occlusion [22, 23], or deliberate extraction of teeth [20, 24–26]. Studies have reported impaired memory and learning ability with increased expression of brain-derived neurotrophic factor (BDNF) and the decreased number of pyramidal neurons in the hippocampus in mice fed on liquid diets [27]. Studies have also reported that cell proliferation in the hippocampus is characteristically inhibited by soft diet feeding in rats [28]. Further, it was shown that loss of masticatory function by deliberate extraction of maxillary molars in young growing mice resulted in chronic stress and malnutrition. These mice developed impaired hippocampal-dependent learning ability, hyperactivation, and lateralized rotation behavior commonly associated with dysfunction of the dopaminergic system [24]. The dopaminergic system plays a vital role in attention and recognition memory in the prefrontal cortex and the hippocampus [24].

Human epidemiological studies have consistently suggested correlations/associations between masticatory impairment and a low number of teeth with the deterioration of cognition and memory [13, 15, 29–32]. Further, magnetic resonance imaging (MRI) studies have confirmed the association between chewing and increased activation of memory centers of the brain [33, 34]. It is also suggested that successful aging, i.e., maintaining high cognitive capacity, might partly be affected by preserving the natural teeth [35]. However, it is also debated whether the associations between the indicators of poor oral health (dentition status, periodontal disease) and cognitive health could be bidirectional. Patients with impaired cognitive function may be more likely to have poorer oral hygiene, resulting in periodontal disease and tooth loss, due to their cognitive problems. On the one hand, several studies investigating oral health (i.e., periodontitis) as an independent risk factor for dementia have had a cross-sectional study design and thereby problems with temporality and reverse causality. Then again, studies do show significant correlations and associations between chewing and cognitive functions. Thus “cause-effect” relationships have yet to be established in humans. Therefore, the question whether the detrimental effect of loss of masticatory function on cognition is reversible through oral rehabilitation remains to be investigated. In the current project, we propose an interventional study to investigate the relationship between mastication and cognition in humans. The specific aim of the study is to investigate the effect of rehabilitation of masticatory function on neurocognitive assessments in older adults.

## Methods/design

### Study location

Patient recruitment will be performed at the Swedish public dental health service, Folktandvården Stockholms Län AB, Sweden. The dental rehabilitation procedures of the recruited study participants and all the cognitive measurements; masticatory ability and masticatory function test and saliva samples will be performed/collected at the Department of Prosthetic Dentistry, Folktandvården Eastmaninstitutet, Stockholm, Sweden. The imaging data will be collected at the Stockholm University Brain Imaging Centre (SUBIC) and analyzed at the Department of Neurobiology, Care Sciences and Society (NVS), Karolinska Institutet, Sweden.

### Study participants

The study will include patients seeking fixed prosthodontic treatment either due to reduced dentition measured by Eichner’s index [36] and complaining of impaired chewing ability due to a reduced number of posterior functional units or reduced dentition in general. Efforts will be made to recruit an equal number of men and women. The criteria for inclusion (Table 1) are patients in the age range of 65–80 years, in need of prosthodontic treatment, and presenting a Mini-Mental State Examination (MMSE) score > 25 [37]. The MMSE is a screening tool that has shown to be a sensitive marker of overt dementia and will therefore help us to discriminate between normal cognitive status and individuals at risk of dementia. However, MMSE is not a cognitive test that is suitable for intervention evaluation because many patients will perform at a maximum or near-maximum level (i.e., ceiling effect), leaving no opportunity to detect improvement across time [38]. On the contrary, our outcome tests with the neuropsychological assessments (NA) are highly sensitive to change (see heading outcome parameters and measurements). Thus, we aim to exclude patients with overt dementias (with low potential of cognitive improvement after intervention), but we remain open to including patients within the cognitive continuum from normal performances to mild cognitive impairments (with higher potential of cognitive improvement by the intervention). Circumstances that could compromise the validity of the tests, such as poor Swedish language skills, reading disabilities, severely reduced hearing or vision, are also considered as a criterion for exclusion, depending on the severity of the condition. Patients without any subjective masticatory dysfunction and patients that will be rehabilitated with removable dentures are excluded. Specific criteria are used to determine eligibility for the (optional) MRI acquisitions (Table 1). The demographic details (height, weight, etc.,) along with self-reports of ongoing medications (if any) and chewing ability are collected. The participants are screened with Alcohol Use Disorders Identification Test (AUDIT) [39, 40] and the oral health-related QoL of the participants is assessed with Oral Health Impact Profile (OHIP-14) [41]. The hospital anxiety and depression (HAD) scale will be used to measure the anxiety and depression in the groups [42]. The number of remaining teeth and occluding units are collected from the dental record (intraoral photos and dental X-rays).

**Table 1 Tab1:** Inclusion and exclusion criteria for study participants

Inclusion criteria	Exclusion criteria
65–80 years of age at the start of the study	Brain trauma or stroke < 6 months
Impaired chewing ability	Neurological disease (stroke, Alzheimer's disease, other dementias, Parkinson's disease)
Missing teeth as indicated by Eichner index B2-B4, C1-C4	Other intellectual disability
Indications for treatment with fixed prosthodontics, implant and/or tooth-supported (overdentures included)	Psychological disorders
Mini-Mental State Examination (MMSE) score > 25	Participants with chronic pain, depression, or sleeping disorders
	Daily analgesic medication that may affect cognitive and/or executive performance of the brain
	Poor Swedish language skills, reading disabilities
	Severely reduced hearing or vision
	*Exclusion criteria* *Magnetic resonance imaging*
	Claustrophobia
	Difficulties in lying down in a supine position for about an hour, or any other difficulties related to the MRI head coil
	Participants with mental or medical implants in the body contraindicating MRI scan

### Sample size

No studies are currently available that directly compare rehabilitation of chewing function with a control condition on neurocognitive measures. We, therefore, designed our RCT as a superiority trial with enough statistical power to detect a difference in outcome between treatments (if present) with a medium effect size (partial eta square, eta2). For the longitudinal analysis that assesses rehabilitation differences, we expect an effect size (partial eta square, eta^2^) on the NA of at least 0.06. With α set to 0.05 and power at 0.80, a sample of 30 participants in each group is required. The power calculation of the repeated measures analysis is estimated with within-participant factors, which also controls for the between-participant variance. However, due to the moderate rate of dropouts (20–25%) observed across different ongoing studies, optional non-participation of MRI screening, and technical difficulties (e.g., movement artifacts) during brain imaging, we estimate that inclusion of 40 participants in each group is required to meet the demands for statistical power. However, only the first 20 participants willing and eligible to participate in the MRI procedures in each group will undergo brain imaging due to practical and logistical reasons. The MRI acquisitions are optional since there are more contraindications medically and patients are more reluctant to participate. By making MRI optional participants can still be included in the study when MRI acquisitions are not feasible.

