**Fig. 1 Fig1:**
[figure not shown]
Overview of the study protocol

The oral rehabilitation of the experimental group will start immediately after the first NA (pre-test). The control group on the other hand will be pre-and post-tested with an interval of about 3 months before the onset of the prosthodontic rehabilitation procedure. The relatively short period between the pre-and post-tests for the control group is motivated by ethical considerations. It is not considered justifiable to deny prosthodontic rehabilitation to the control group any longer than 3 months. Therefore, it is likely that the time between pre-and post-test for the control group will be slightly shorter than for the experimental group. We aim to statistically control for time differences by including time between pre-and post-test as a covariate of interest in the model. Both the experimental and the control group will also perform the post-tests (see Table 2) on two occasions after the completion of the oral rehabilitation procedures (Fig. 1). The first post-test occasion is after at least 3 months and the second test is to be conducted at 1-year follow-up, approximate time needed to adapt to the new fixed prosthesis.

**Table 2 Tab2:** Outcome measures

	Variable	Method/test	Measurements
*Primary outcome variables*			
1	Neuropsychological assessments	Episodic memory	BVMT-R
*Secondary outcome variables*			
2	Chewing function	Two-color chewing gum mixing test	VOH scores
3	Oral health	Oral health impact profile (OHIP) 14	OHIP score
4	Stress	Salivary test Hospital and anxiety depression scale questionnaire	Salivary Cortisol HAD score
5	Dentition status	Dental records, photos and X-rays	Eichner’s index Number of teeth Number of occluding units
6	Brain scans	Magnetic Resonance Imaging	Volume change hippocampus and/or total volume change gray matter

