### Statistical methods

The data from the study will be entered in a Microsoft Excel sheet and exported to statistical software packages like SPSS Inc, Statistica, StatSoft Inc, or similar advanced analytics software packages for analysis. The result from the cognitive testing will be analyzed as repeated measure Analysis of covariance (ANCOVAs) with groups (experimental and control) and time (pre-and post-rehabilitation) as factors. Group-by-time interaction, the main effect of the group, and the main effect of time will be evaluated. To compare the magnitude of gains, the effect size (partial eta-square) will also be calculated. We will use time-length between pre-and post-tests as a covariate of interest with aiming to better control group differences. To predict the intervention outcomes, we will develop models that mainly predict cognitive test measures (NA). Predictive ability is defined as the amount of variance in the outcome that can be explained by pre-test cognitive status (slope method). Explained variance in the outcome will be obtained by analyzing linear regressions.

Preprocessing and statistical analyses of MRI data will be performed with Statistical Parametric Mapping (SPM) run in MATLAB (MathWorks). Movement correction will be performed by realigning and unwarp to the first image in the series. To consider group-specific anatomical brain differences, all patients will be normalized to Montreal Neurological Institute (MNI) echoplanar-imaging template. However, cortical thickness measures will not be normalized but rather used in their raw form. For cortical segmentation, a Freesurfer pipeline will be applied to the MRI images to produce regional cortical thickness and volumetric measures. To investigate rehabilitating-related changes repeated measures ANCOVAs will be performed with the groups (experimental and control) and time (pre-and post-rehabilitation) as factors. We will control for multiple comparisons with the Bonferroni-Holm method since all cognitive tests are correlated and because a majority of the test variables in this study belong to the same family (cognitive domain) or even the same test. In case of significant behavioral effects (i.e., a significant group-by-time interaction effect indicating that: the experimental group improves their cognitive performances > the control group), the changes will be evaluated as covariates of interest in relation to the potential brain changes.

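### The 30 per group cannot be reproduced from the stated inputs; if 0.06 is the partial eta-squared of the planned group-by-time interaction, power is about 49%, not 80%

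*Protocol article*

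**What the plan says.** All the sample size inputs are in one paragraph of the protocol article, under Sample size. For the longitudinal analysis of rehabilitation differences, "we expect an effect size (partial eta square, eta^2^) on the NA of at least 0.06". It continues: "With α set to 0.05 and power at 0.80, a sample of 30 participants in each group is required". The method is described in one sentence: "The power calculation of the repeated measures analysis is estimated with within-participant factors, which also controls for the between-participant variance". Enrolment is then raised to 40 per group for dropout of 20–25%, optional non-participation in MRI, and technical problems during imaging.

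Under Statistical methods, the cognitive results are analysed by repeated measures ANCOVA "with groups (experimental and control) and time (pre-and post-rehabilitation) as factors. Group-by-time interaction, the main effect of the group" and the main effect of time are evaluated. The same section adds: "To compare the magnitude of gains, the effect size (partial eta-square) will also be calculated". Further on, it treats a significant group-by-time interaction as the sign that the experimental group improved more than the control group.

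The article does not give the effect for which power was calculated (time or group-by-time), the number of occasions entered, the sidedness, the assumed correlation between repeated measures, or how 0.06 was converted for the calculation.

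**The concern.** With two groups and two occasions, the interaction has one degree of freedom and is equivalent to a t-test on change scores. Its partial eta-squared is computed against within-participant error, so any gain from repeated measurement is already inside the 0.06. Read that way, 0.06 is a standardised difference in change of about 0.5, and 30 per group is far too few for 80% power.

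The trial is described as having enough power for a medium effect, on the battery that contains the primary outcome. If the literal reading is the intended one, 30 completers per group would miss an effect of that size about half the time.

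**Working it through.** **Inputs.** Alpha 0.05, target power 0.80, 30 per group (N = 60) and partial eta-squared 0.06 come from Sample size. The 2 × 2 design and the interaction test come from Statistical methods. Sidedness is not stated; a two-sided F test is assumed.

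**Step 1: try to reproduce 30 per group on the literal reading.**
- f² = 0.06/(1 − 0.06) = 0.0638, so f = 0.2526 and d = 2f = 0.505 in SDs of change.
- λ = N·f² = 60 × 0.0638 = 3.83. Noncentral F with 1 and 58 df gives power **48.6%**.
- Variants: λ = (N − 2)·f² gives 47.3%; the normal approximation gives 49.9%; one covariate (57 error df) gives 48.6%; a one-sided test gives 61.4%. None reaches 80%.
- 40 per group, no dropout: λ = 80 × 0.0638 = 5.11, power **60.7%**.
- The first n with at least 80% is **63 per group** (λ = 126 × 0.0638 = 8.04, power 80.3%), or 64 with the (N − 2) form.
- At N = 60, 80% power is reached at partial eta-squared 0.119. Then f² = 0.1192/0.8808 = 0.1353 and d = 2√0.1353 = **0.74**.

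The stated inputs alone therefore do not give 30.

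**Step 2: Cohen's f in a within-between routine, two occasions.** Here λ = N·2·f²/(1 − ρ), with 1 and 58 df at N = 60. The interaction's own partial eta-squared is q/(1 + q), where q = 2f²/(1 − ρ).

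| ρ | Power at N = 60 | Total N for 80% | Interaction partial eta-squared |
|---|---|---|---|
| 0 | 77.7% | 64 | 0.113 |
| 0.05 | 79.7% | 62 | 0.118 |
| 0.10 | 81.8% | 58 | 0.124 |
| 0.30 | 90.2% | 46 | 0.154 |
| 0.50 | 97.1% | 34 | 0.203 |
| 0.70 | 99.9% | 22 | 0.299 |

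Power at N = 60 is exactly 80% at ρ = 0.056, so a total of 60 corresponds to ρ of about 0.05–0.10. At those values the effect powered for is an interaction partial eta-squared of about 0.12, twice the stated 0.06. At higher correlations it is larger still.

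**Step 3: more than two occasions.** On the partial eta-squared convention, λ = f²·(N − 2)(m − 1) with (m − 1) and 58(m − 1) df. Three occasions give 67.0% (total N for 80% is 80). Four occasions give λ = 0.0638 × 58 × 3 = 11.1 and power 79.8%, close to the stated figure. With Cohen's f and three occasions, power is 85.9% at ρ = 0 and 99.2% at ρ = 0.5.

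**Step 4: from 30 to 40.** 30/0.80 = 37.5, so 38; 30/0.75 = 40. The upper dropout figure alone gives 40 per group, with nothing left for MRI losses to explain.

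**The case against.** The strongest reply is that the article says what kind of calculation was done: a repeated measures one with within-participant factors. Power then depends on the correlation, the number of occasions and the effect-size convention. An article that condenses a fuller protocol may omit these. Across the variants above, 30 per group gives anything from about 47% to over 99%, and some variants land on 80%. At correlations of 0.5–0.7 on the Cohen's f convention, 30 per group is more than enough. Failing to land on 30 there is no sign of too little power.

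Much of this stands. A reader might infer that the stated 80% is simply wrong and the trial underpowered. The document does not support that unconditionally, because the convention is not given.

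The routes that return 80% nevertheless fit the text poorly:
- A correlation of 0.05–0.10 sits badly with the good reliability and minimal measurement error claimed under Outcome parameters and measurements.
- Four occasions match only the control group, with its extra test before rehabilitation. For the later tests, "Both the experimental and the control group will also perform the post-tests (see Table 2) on two occasions after the completion" of rehabilitation, which gives the experimental group three occasions in all. Statistical methods names only pre and post, and the Discussion expects the groups to be similar at post-test 2.

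A reader might also infer that the MRI part fails its own requirement, because "only the first 20 participants willing and eligible to participate in the MRI procedures in each group will undergo brain imaging". The document does not support that either. The 0.06 and the 30 are set for the neuropsychological assessments, MRI is a secondary outcome, and the cap is disclosed as logistical and, in the Discussion, as a possible weakness. What remains is loose wording: MRI losses are listed as a reason for 40 per group when they change no number. It would also be speculation to say how a null result would be read; the article does not address it.

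**Conclusion.** The point holds in conditional form. The figure of 30 per group is not reproducible from what is stated. The shortfall, 49% against a claimed 80%, rests on two assumptions: that 0.06 is the partial eta-squared of the pre/post group-by-time interaction, and that the test is two-sided. The first is the literal reading of Sample size together with Statistical methods.

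On the two-occasion Cohen's f convention, power may be 80% or well above, but the 0.06 is then not on the scale that Statistical methods says will be reported. Either way, a reader who takes the paragraph to mean 80% power for a reported partial eta-squared of 0.06 on the planned two-occasion test is misled by a factor of about two in the effect size. It should be corrected because the power claim concerns the trial's main comparison and restating it is cheap.

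**What to change.** Keep enrolment at 40 per group. In Sample size, state the effect tested, the number of occasions, the sidedness, the effect-size convention and the assumed correlation between repeated measures.

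Restate the power to match the planned pre/post group-by-time test: with 30 completers per group, about 49% for an interaction partial eta-squared of 0.06, and 80% for about 0.12 (standardised difference in change about 0.74). If the sponsor can show that another convention was used, report that calculation instead, with its inputs and the interaction partial eta-squared it implies.

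As a minor wording change, drop MRI losses from the reasons for 40 per group, since dropout alone accounts for it.

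The cost is a few sentences and no extra participants. The stated power will look less favourable if the literal reading is confirmed.

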### Intervention: oral rehabilitation

Individual treatment options will be discussed with the patients and rehabilitation will be provided depending on the clinical situation and the patient’s financial status. The rehabilitation will include fixed prosthodontics and will be achieved by providing the latest and most effective measures in modern-day prosthodontics. Briefly, the procedures will involve a control phase involving scaling, root planning, oral hygiene instructions, etc. When needed, extractions and bone augmentation will be performed, and also temporary removable dentures will be made if required. This will be followed by the restoration of the vertical dimension with occlusal splints (if needed), tooth preparations, placement of dental implants (if needed), and finally cementation of dental crowns. The entire rehabilitation phase is estimated to take approximately 3–12 months, where implant treatment is the main factor for the longer time frames.

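### The primary pre/post repeated-measures ANCOVA does not condition on baseline, so unequal dropout between arms with very different waits to the first post-test could bias it, and the sample-size allowance treats dropout as equal

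*Protocol article*

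**What the plan says.** **Analysis.** The Statistical methods section analyses the cognitive tests by "repeated measure Analysis of covariance (ANCOVAs) with groups (experimental and control) and time (pre-and post-rehabilitation) as factors". Baseline is therefore a level of the time factor. The only covariate named is the length of the interval between pre- and post-test.

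**Timing.** Under Study design, the control arm is tested twice about 3 months apart, before any treatment, because "It is not considered justifiable to deny prosthodontic rehabilitation to the control group any longer than 3 months"; the Discussion allows 3 to 4 months. The experimental arm starts treatment right after its pre-test and has its first post-test at least 3 months after treatment ends. On treatment length, the Intervention section says: "The entire rehabilitation phase is estimated to take approximately 3–12 months". Study design nevertheless describes the control interval as only a little shorter than the experimental one.

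**Dropout.** The Sample size section states "With α set to 0.05 and power at 0.80, a sample of 30 participants in each group is required". It then cites one loss rate, "due to the moderate rate of dropouts (20–25%) observed across different ongoing studies", together with MRI non-participation and imaging problems, and concludes: "we estimate that inclusion of 40 participants in each group is required to meet the demands for statistical power". It does not distinguish between the arms.

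**The concern.** The Discussion places the main comparison at the experimental arm's first post-test against the control arm's pre-treatment post-test. Before that point the experimental arm must complete treatment that may include extractions, bone augmentation and implants, and that depends partly on what the patient can pay. The control arm has only to return after about 3 months. The arms therefore differ in both the length and the nature of their exposure to loss.

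With two occasions, the group-by-time term is the difference in mean change among people who have both scores. If the completers in one arm are selected on baseline memory and those in the other are not, or less so, regression to the mean alone produces a difference in change. This matters here because the Study participants section deliberately recruits from normal performance to mild impairment, so baseline scores will be spread out. It also expects more room for improvement at the impaired end.

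At stake is the reading of the primary result. The Discussion treats the unequal interval only as a type 2 error risk and says a positive result would support firm conclusions. Selective loss can bias the contrast in either direction, so that assurance does not follow.

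**Working it through.** **1. The plan's own allowance.** 30/(1 − 0.25) = 40 and 30/(1 − 0.20) = 37.5, rounded up to 38. The figure of 40 reproduces at 25% loss. With equal loss, 40 enrolled leave 40 × 0.80 = 32 or 40 × 0.75 = 30 per arm. At 25% there is no margin. I take the 30 per group as given.

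**2. Time to the first post-test.** Experimental: 3 + 3 = 6 months to 12 + 3 = 15 months. Control: about 3 months. The ratio is 2 to 5.

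**3. Numbers left if loss follows time at risk (assumption).** The document gives no split by arm. Assume a constant monthly hazard h, the same in both arms, with average loss D by the first post-test. Solve ½[(1 − exp(−hT)) + (1 − exp(−3h))] = D for experimental interval T. Power is for a two-sided two-sample t-test on change, with the effect set so that 30 v 30 gives exactly 0.80 (0.736 SD of change).

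| D | T (months) | h | Loss exp. / control | Left of 40, exp. / control | Power |
|---|---|---|---|---|---|
| 20% | 6 | 0.050 | 26.0% / 14.0% | 29.6 / 34.4 | 0.82 |
| 20% | 9 | 0.038 | 29.1% / 10.9% | 28.3 / 35.7 | 0.82 |
| 20% | 15 | 0.026 | 32.5% / 7.5% | 27.0 / 37.0 | 0.82 |
| 25% | 6 | 0.065 | 32.3% / 17.7% | 27.1 / 32.9 | 0.80 |
| 25% | 9 | 0.050 | 36.1% / 13.9% | 25.6 / 34.4 | 0.79 |
| 25% | 15 | 0.034 | 40.2% / 9.8% | 23.9 / 36.1 | 0.78 |

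The total stays at 60 to 64, which is why power barely moves. In the extreme case of all loss in the experimental arm, 24 v 40 gives 0.80 and 20 v 40 gives 0.75.

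**4. Bias of the change contrast (assumption: 35% experimental loss, 10% control loss, no true effect).** Let Z be the standardised baseline and let the post-test have correlation ρ with it and the same SD. Among completers the expected change is −(1 − ρ) × E(Z | completer). The bias is therefore

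bias = −(1 − ρ) × (m_E − m_C),

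where m_E and m_C are the mean baselines of completers in the two arms. Loss follows a logistic model in Z with slope b per SD (low scorers leave more often) and an intercept set to give 35% or 10%.

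| b (odds ratio per SD) | m_E | m_C, same b in control | Bias, ρ = 0.5: same b / control loss random | Bias, ρ = 0.7: same b / control loss random |
|---|---|---|---|---|
| 0.25 (1.28) | 0.086 | 0.025 | −0.03 / −0.04 | −0.02 / −0.03 |
| 0.5 (1.65) | 0.166 | 0.049 | −0.06 / −0.08 | −0.04 / −0.05 |
| 1 (2.72) | 0.292 | 0.091 | −0.10 / −0.15 | −0.06 / −0.09 |

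Example: b = 1, ρ = 0.5, control loss random (m_C = 0): −0.5 × 0.292 = −0.146. If high scorers leave instead, the signs reverse.

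**5. Effect of conditioning on baseline.** Where loss depends on baseline, the regression of post-test on baseline is the same in completers as in everyone, so the adjusted contrast has no bias from this source. In simulation (4,000 runs, 40 per arm) the adjusted bias was 0.002 and −0.002, against −0.086 (ρ = 0.7) and −0.146 (ρ = 0.5) for change. Adjustment also helps with no dropout at all. Residual variance falls from 2(1 − ρ) to 1 − ρ², a ratio of (1 + ρ)/2: 0.75 at ρ = 0.5 and 0.85 at ρ = 0.7, a saving of 25% and 15%.

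**The case against.** Four points can be made on the other side.

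- **The split by arm is not documented.** The Sample size section gives one pooled rate, with no arm and no time point, and it may cover follow-up to one year. Patients come seeking treatment, so controls left waiting may also leave early, and the Discussion says overdentures were included partly to help retention. This stands. A reader might infer that dropout will fall mainly on the experimental arm and leave it with fewer than 30. The document does not support that as a fact: equal loss at the stated rates leaves 30 to 32 per arm, and the lower figures depend on the constant-hazard assumption.
- **Power is hardly affected.** This also stands. A reader might see a sample-size failure here, but losses in one arm are offset by retention in the other.
- **The bias depends on strong selection.** The value of −0.15 SD needs an odds ratio of about 2.7 per baseline SD in the experimental arm and none in control. Dropouts would then score about 0.29 + 0.54 = 0.83 SD below completers. With weaker dependence the bias is small. When low scorers leave, it works against finding a benefit. This stands, and is why a range with both directions is given.
- **Missing-data handling may be in an analysis plan not shown.** This stands too: silence about missing post-tests, or about sensitivity analyses, is no finding. It does not dispose of the point, because the article itself fixes the model, and a better one is available from data already being collected.

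The interval covariate is no answer. It does not adjust for baseline selection, and on the documented timings (about 3 months against at least 6) it nearly coincides with arm.

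**Conclusion.** The point holds as a conditional risk of selection bias. Three things rest on the document: the model as fixed does not condition on baseline, the time to first post-test differs by a factor of 2 to 5, and the dropout allowance ignores that difference and has no margin at 25%. The size rests on assumptions. With 35% against 10% loss, logit slopes of 0.25 to 1 per baseline SD and correlations of 0.5 to 0.7, the bias is about 0.02 to 0.15 SD, and its sign depends on who leaves. Without a link between loss and baseline or outcome, this bias does not arise. Under a constant hazard the experimental arm keeps about 24 to 30 of 40 and control about 33 to 37. The change is worth making because it costs little and improves precision even if dropout turns out equal.

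**What to change.** **Statistical methods.** For BVMT-R, replace the repeated-measures ANCOVA with a likelihood-based linear mixed model on all randomised participants and all available visits, with the baseline mean constrained equal across arms. An ANCOVA of post-test on baseline BVMT-R is an acceptable simpler alternative. Take the arm contrast at the first post-test as the primary result. This deals with loss that depends on observed scores; it does not remove bias from loss that depends on unobserved scores, nor the difference in interval itself.

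**Sample size.** State that the allowance from 40 to 30 per group assumes equal dropout, and give the expected numbers per arm if loss is higher in the experimental arm.

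**Cost.** Slightly more analysis work in standard software, and a slightly less favourable expected number in the experimental arm. Visits, tests and treatment are unchanged.
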